**The efficacy of aqueous olanexidine compared to alcohol-based chlorhexidine for surgical skin antisepsis on incidence of surgical site infections in clean-contaminated surgery: a randomised superiority trialTracking Number: UMIN 000049712**

1. GENERAL CONVENTIONS IN STATISTICAL ANALYSIS
   1. Interim Analysis

No interim analysis will be done in this trial.

- 1. Data Monitoring Committee

Data Monitoring Committee will be held to ensure the safety of the trial subjects in accordance with a separate set of operating procedure.

- 1. Handling of Missing Data

Unless otherwise noted, withdrawn or missing data will not be replaced with substituted values created by statistical imputation.

- 1. Data Transformation

In case of change of variables such as square root or logarithm, precise procedure will be described in the statistical analysis plan.

- 1. Significance Level and Confidence Interval

Unless otherwise noted, results from all analysis will be assessed against the significance level(α) of 0.05 and the confidence interval (CI) of 0.95 as two-sided test.

- 1. Multiplicity Adjustment

Unless otherwise noted, statistical adjustments for multiplicity will not be performed in this trial.

- 1. Subgroup Analysis

Not applicable

- 1. Data Processing Conventions

**Definitions of days and period**

- In calculation of the number of days, the beginning date will be subtracted from the final date and then one day will be added.

(examples)

- Days dosed: If dosing is ended on the first date dosed , the dosing period will be counted as one day.
- Days to the occurrence of an adverse event(AE): If an AE occurs next day after the first date dosed, the period to the onset of the AE will be counted as two days.
- Survival period：If death occurs next day after the first date dosed, the survival period will be counted as two days.
- The number of days will be calculated as follows:
- One year: 365.25 days
- One month:30.4375 days
- One week: 7 days
- In counting the number of days after the initial date as follows:
- The initial date dosed: day (1)
- Next day after the initial date: day(2)
- Two days after the initial date: day(3)

The following days will be treated as the same.

- One day before the initial date dosed: day (-1)
- Two days before the initial date: day(-2)
- Three days before the initial date: day(-3)

The following days will be treated as the same.

**Handling of digits after the decimal point**

- One digit lower than the raw data values will be added to provide the values of mean, standard deviation, and median. (The values will be rounded at the next digit.)
- All percentages should be rounded and reported at a single decimal place (e.g.12.3%)。
- In calculating mean, standard deviation, and/or median for statistical analysis, rounding will not be performed before the final calculation but only for the final results.

**Confidence Interval (CI) for the incidence rate**

Confidence interval of incidence rate (or incidence percentage), response rate (or response percentage) will be calculated by correct method with F distribution.

The number of population for analysis will be defined as N, and the number of patients in whom the events occurred, or the number of responders to the treatment as X. The response rate*(p)* , the upper limits (*pu*), or lower limits(*p_L_*) of the confidence interval of 100 (1 – *α*)% at a two sided-test, will be calculated by the following equations. 95% confidence interval reflects α of 0.05.

$$p=\frac{X}{N},$$

$$p_{U}=\left( 1+\frac{N-X}{(X+1)F\left( 1-\frac{\alpha}{2},2(X+1),2\left( N-X \right) \right)} \right)^{-1},$$

$$p_{L}=\left( 1+\frac{N-X+1}{X F\left( 1-\frac{\alpha}{2},2X,2\left( N-X+1 \right) \right)} \right)^{-1}.$$

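### The SAP's exact confidence-interval formula takes the wrong F quantile for the lower limit, so the interval excludes the observed rate

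*SAP*

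**What the plan says.** The rule is in the SAP under the data processing conventions of section 1, headed Confidence Interval (CI) for the incidence rate. It covers incidence and response rates, whose intervals "will be calculated by correct method with F distribution". N is the number analysed, X is the number with the event or response, and the estimate is p = X/N.

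Two equations follow, and the text says the limits are calculated from them:

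- The upper limit contains "F\left( 1-\frac{\alpha}{2},2(X+1),2\left( N-X".
- The lower limit contains "F\left( 1-\frac{\alpha}{2},2X,2\left( N-X+1".

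The section states that the "95% confidence interval reflects α of 0.05". The general conventions also ask for "the confidence interval (CI) of 0.95 as two-sided test". The SAP does not say which tail F(1 − α/2, ·, ·) refers to, and no other section restates or corrects the equations.

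**The concern.** The layout and the degrees of freedom are those of the Clopper-Pearson interval. In that interval the two limits come from opposite tails. Here both take the same quantile level, in the same position in the formula, so both limits fall on the same side of the estimate.

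This is the only rule the SAP gives for the confidence interval of a single rate. Any arm-level interval for surgical site infection, reoperation or toxicity and allergy events would fall under it. A programmer who follows the equations produces narrow intervals that do not contain their own estimates. One who notices the fault and uses something else departs from the plan without a record of it.

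**Working it through.** **Inputs.** α = 0.05, two-sided, and the two printed equations, all from the SAP. The SAP gives no sample size, event count or worked example, so there is no stated figure to reproduce. The counts below are assumptions for illustration.

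**Formulas as printed**, with F(q; a, b) read as the lower-tail q quantile:

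- p_U = 1 / [1 + (N − X) / ((X + 1) · F(1 − α/2; 2(X + 1), 2(N − X)))]
- p_L = 1 / [1 + (N − X + 1) / (X · F(1 − α/2; 2X, 2(N − X + 1)))]

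**Exact lower limit:** the same expression as p_L with F(α/2; 2X, 2(N − X + 1)). Equivalently, replace the F term by 1 / F(1 − α/2; 2(N − X + 1), 2X).

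**Example, X = 30, N = 300, p = 10.0%:**

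- Upper limit as printed: F(0.975; 62, 540) = 1.4140. 270 / (31 × 1.4140) = 6.160, so p_U = 1/7.160 = 13.97%. This is the exact upper limit.
- Lower limit as printed: F(0.975; 60, 542) = 1.4204. 271 / (30 × 1.4204) = 6.360, so p_L = 1/7.360 = 13.59%. This is above the estimate.
- Lower limit with α/2: F(0.025; 60, 542) = 0.6642. 271 / (30 × 0.6642) = 13.600, so p_L = 1/14.600 = 6.85%. This is the exact lower limit.

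**Other counts:**

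| X/N | Estimate | As printed | Exact |
|---|---|---|---|
| 3/300 | 1.0% | 2.4% to 2.9% | 0.2% to 2.9% |
| 15/300 | 5.0% | 7.7% to 8.1% | 2.8% to 8.1% |
| 30/300 | 10.0% | 13.6% to 14.0% | 6.8% to 14.0% |
| 60/300 | 20.0% | 24.6% to 25.0% | 15.6% to 25.0% |
| 10/100 | 10.0% | 16.4% to 17.6% | 4.9% to 17.6% |

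**Why this is general.** Put X − 1 in place of X in the printed p_U: X + 1 becomes X and N − X becomes N − X + 1. The result is exactly the printed p_L. The plan's lower limit for X events is therefore the upper limit for X − 1 events, and the interval only spans the gap between two neighbouring upper limits. For N = 10, 50, 100, 300 and 600, with every X from 1 to N − 1 (9 + 49 + 99 + 299 + 599 = 1055 pairs), the printed p_L exceeded X/N in all 1055.

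**Coverage.** For true rates of 5%, 10% and 20% with N = 100 or 300, the printed interval covers the true rate with probability 1.0% to 3.4%. The corrected interval covers it with probability 95.6% to 98.3%.

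**The other reading of F.** If F(1 − α/2, ·, ·) means the point with probability 1 − α/2 above it, p_L becomes exact but p_U fails. For 30/300, the quantile in p_U is then 0.6686. 270 / (31 × 0.6686) = 13.03, so p_U = 1/14.03 = 7.1% and the interval is 6.8% to 7.1%. Under this reading p_U fell below X/N in all 1055 pairs.

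**Boundaries.** At X = 0 the printed p_L divides by zero. At X = N the printed p_U has zero degrees of freedom. The SAP sets no convention for either case.

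**The case against.** The algebra is not in dispute; the objections concern reach and consequence.

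- *The trial's main result does not depend on this.* That stands. The SAP's sections on the primary and secondary endpoints specify Mantel-Haenszel adjusted risk ratios, their intervals and tests, and the subgroup section uses the Mantel-Haenszel test. None of these uses the faulty equation. No analysis section asks for a single-arm interval by name; the rule is a general convention that applies wherever one is reported.
- *The harm arises only if someone codes the equations by hand.* A standard exact routine would avoid it, and a lower limit above the estimate would be conspicuous in the first table. That is fair as a judgement of likelihood. However, the SAP prescribes the equations and names only the software, SAS 9.4 or higher, not a routine.
- *The fault does not affect every possible count.* This is right. At X = N the printed p_L is just below 1 (0.9999 for 300/300), and at X = 0 it is undefined. For rare events the width is small but not negligible relative to the rate: 1/100 gives 3.6% to 5.4%. The claim holds for 0 < X < N.
- *The boundary cases are not evidence of the quantile error.* This is also right. The correct F form has the same gaps, which are closed by convention, so they are a secondary omission.
- *The equation could have been damaged in conversion from PDF.* This cannot be excluded outright, but both expressions are complete and well formed, and nothing suggests that a term was lost.

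**Conclusion.** The concern holds. For 0 < X < N the printed equations cannot both be right under one definition of F. Under the natural reading, which makes the upper limit exact, the lower limit exceeds the observed rate. The 30/300 interval is then about 0.4 percentage points wide (13.97 − 13.59 = 0.38), against 7.1 points for the exact interval (13.97 − 6.85 = 7.12). The sizes depend on illustrative counts; the direction does not. The error is confined to intervals for single rates and leaves the Mantel-Haenszel treatment comparisons untouched. It is nevertheless a prespecified rule that gives a wrong result when followed.

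**What to change.** Replace the lower limit by p_L = 1 / [1 + (N − X + 1) / (X · F(α/2; 2X, 2(N − X + 1)))], leave the upper limit as it is, and state that F(q; ·, ·) is the lower-tail q quantile. Add that p_L = 0 when X = 0 and p_U = 1 when X = N. Alternatively, delete the equations and specify exact Clopper-Pearson limits from the BINOMIAL option of SAS PROC FREQ.

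Either way, name the method as exact (Clopper-Pearson) and check the program against one worked case, such as 30/300 giving 6.85% to 13.97%. The SAP's revision history shows a version prepared for peer review, so any single-rate intervals already produced should be compared with a standard exact routine. The cost is one corrected formula and a short program check, with no effect on trial conduct or on the primary analysis.

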1. ANALYSIS
   1. Definitions of Population
      1. Full Analysis Set (FAS)

FAS is defined as all enrolled subjects who do not undergo surgery or who withdrew consent before the assessment of the primary endpoint will be excluded.

- - 1. Per Protocol Set (PPS)

The PPS will exclude all subjects in the FAS population who meet any of the following major violations of the protocol.

- Inclusion criteria violation
- Exclusion criteria violation
- Prohibited concomitant drug use violation
- Prohibited concomitant therapy violation
  - 1. Intention-to-trea Set (ITT)

The ITT will include all subjects who were randomly assigned.

- - 1. Safety Analysis Set (SAF)

Safety analyses will be performed on the SAF population subjects who are enrolled in the trial and applied the assigned disinfectant at least once for each treatment group.

- 1. Analysis Principles

The primary analysis for all efficacy endpoints will be performed on the FAS while the analyses on the PPS and ITT will be treated as reference data. Safety analyses will be performed on the SAF.

1. **DEMOGRAPHIC AND BASELINE CHARACTERISTICS**

Demographic and other baseline characteristic will be summarized by assigned treatment group with descriptive statistics. Continuous variables will be summarized with demographic statistics (number of patients(n), mean, standard deviation, min, max, and median).

Categorical variables will be summarized by frequencies and percentages according to assigned treatment group. A t-test or Wilcoxon’s rank-sum test will be used for comparison of treatment group with continuous variables. Fisher’s exact test will be used with categorical data.
Results from all analysis will be assessed against the significance level (α) of 0.05 at two-sided test.

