1. ANALYSIS OF EFFICACY
   1. Analysis Plan for Primary Endpoints

Primary efficacy endpoint is postoperative 30-day SSI. To compare the treatment effects, the adjusted risk ratio and its 95% CI will be estimated using the Mantel-Haenszel method. To test for a significant association with the primary outcome, the Mantel-Haenszel test will be applied after the adjustment for allocation factors.

- 1. Analyses Plan for Secondary Endpoints

The analyses of the secondary efficacy endpoints will be performed to support the discussion on the results of the primary analysis in this trial. Multiplicity adjustment will not be performed in this trial in assessing secondary endpoints.

To compare the treatment effects, the adjusted risk ratio and its 95% CI will be estimated using the Mantel-Haenszel method. To test for a significant association with the primary outcome, the Mantel-Haenszel test will be applied after the adjustment for allocation factors.

Secondary efficacy endpoints

The Mantel-Haenszel test will be applied after adjusting for allocation factors.

1. **Postoperative 30-day superficial incisional SSI rate**
2. **Deep incisional SSI rate, organ/space SSI rate**
3. **Rate of positive bacterial wound culture, and their strains**
4. **Bacterial strain**
5. **Toxicity and allergies events (erythema, symptoms of allergy) rate.**
6. **Reoperation rate due to SSI**

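### The safety set leaves out patients prepared only with the other arm's antiseptic, and the SAP does not say which set governs the toxicity and allergy endpoint

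*SAP*

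**What the plan says.** The SAF definition (section 2.1.4) covers subjects who are "enrolled in the trial and applied the assigned disinfectant at least once for each treatment group". The Analysis Principles (section 2.2) then say: "Safety analyses will be performed on the SAF".

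For efficacy, section 2.2 says: "The primary analysis for all efficacy endpoints will be performed on the FAS while the analyses on the PPS and ITT will be treated as" data for reference. The FAS definition removes subjects "who do not undergo surgery or who withdrew consent before the assessment of the primary endpoint will be excluded". That sentence is grammatically incomplete, but its exclusions are clear, and receiving the wrong product is not one of them. The ITT set keeps everyone randomised.

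The list under Analyses Plan for Secondary Endpoints, headed as efficacy endpoints, has as its item 5: "Toxicity and allergies events (erythema, symptoms of allergy) rate".

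**The concern.** The harms that the SAP names, erythema and allergic symptoms, depend on which product touched the skin. A safety set should therefore contain every exposed patient, grouped by actual exposure. Here membership depends on having received the allocated product. A patient prepared only with the other product fails that condition despite having been exposed.

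The endpoint list adds a second difficulty. The toxicity and allergy rate is a safety outcome by nature and an efficacy endpoint by listing. The first route leads to the SAF and the second to the FAS, and the two sets treat a wrong-product patient differently. One reaction could be absent from the SAF tables and, in the FAS analysis, set against a product that was never applied to that patient.

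**Working it through.** The SAP gives no figure to reproduce: no sample size, wrong-product count or reaction rate appears in it. The check is to apply the written rules case by case.

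**Inputs.** SAF rule: section 2.1.4. FAS, PPS and ITT rules: sections 2.1.1 to 2.1.3. Set for each type of analysis: section 2.2. Toxicity and allergy endpoint: item 5 of the secondary endpoint list.

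| Product applied | In SAF? | In FAS (operated, consent kept)? |
| --- | --- | --- |
| Allocated product only | Yes | Yes |
| Other arm's product only | No, under either arm | Yes |
| Both | Yes, since the allocated one was applied | Yes |
| Neither | No | Yes |

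The second row is the problem: the patient was exposed but is outside the safety set. The fourth row is correct for a safety set. In the third row the patient is included, but the SAP does not say in which group.

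**Does another rule repair the second row?**

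- No section of the SAP at hand says that exposure to either product qualifies, or that safety is grouped by product received.
- The FAS and ITT keep the patient, but neither definition mentions the product received. Grouping by allocation is the natural reading for those sets, and it would place the reaction in the arm whose product was not used.
- The PPS list of major violations covers eligibility and prohibited concomitant drugs or therapies. Use of the wrong disinfectant is not named. Unless the protocol classes it under one of those headings, such a patient can stay in the set meant to reflect adherence while being dropped from the set meant to reflect exposure.

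**Which set governs item 5?** By its place in the list, the FAS. By its content, the SAF. The SAP text at hand does not choose.

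**Illustration of size.** All inputs here are assumptions: 300 patients per arm, 1% to 3% prepared only with the other product, and a 1% reaction rate.

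- Patients lost from the SAF per arm: 300 × 0.01 = 3 to 300 × 0.03 = 9.
- Expected reactions lost per arm: 3 × 0.01 = 0.03 to 9 × 0.01 = 0.09.
- Chance of losing at least one reaction per arm: 1 − 0.99³ = 0.030 to 1 − 0.99⁹ = 0.086.
- With all patients kept, the arm has 300 × 0.01 = 3 reactions, a rate of 3/300 = 1.00%.
- If no reaction is lost, the rate becomes 3/297 = 1.01% to 3/291 = 1.03%, a relative shift of about 1% to 3%.
- If one is lost, it becomes 2/297 = 0.67% to 2/291 = 0.69%, a relative fall of about a third. On these assumptions that has a chance of only about 3% to 9% per arm.

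**The case against.** The strongest objection is that these reactions are not lost from the trial report. Item 5 is an efficacy endpoint by listing, so the FAS applies. The FAS has no wrong-product exclusion, and the ITT analysis is available as reference. A reader might infer from the SAF wording that such reactions are counted for no arm at all. That is not supported: it holds for the SAF analyses, but not necessarily for the analysis of item 5. What the objection does not answer is attribution, because no grouping by product received is stated there either.

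Three other stronger readings also go beyond the document:

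- *Anyone who received the other product drops out.* No. A patient who received both meets the SAF condition. That such a patient is counted in the allocated arm is a natural inference, but the SAP does not state it.
- *Use of the other product is selective, for instance because of known skin sensitivity, so the losses are unbalanced.* Nothing in the SAP supports this. Whether it could happen depends on eligibility and conduct rules that a protocol would hold.
- *A lost event would shift an arm's rate by a third.* This is correct arithmetic on assumed figures, but it describes an unlikely outcome even on those figures.

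It can also be said that the definition is merely clumsy and that any sensible analyst would include all exposed patients. The sentence is indeed awkward, and its closing reference to treatment groups sets no grouping rule. But the condition on the allocated product is explicit, so inclusion of the other exposed patients would depart from the written rule.

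**Conclusion.** The point holds in a limited form. As written, the SAF leaves out a randomised patient prepared only with the other arm's product, although that patient was exposed to a trial antiseptic. The SAP also leaves open whether the FAS or the SAF governs the toxicity and allergy rate, and it states no grouping by product received for either. If the endpoint is analysed on the FAS by allocation, the patient's reaction is counted against the wrong product.

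The size cannot be derived from the SAP. It is nil if no patient received only the other product, and probably small if such patients were rare. The illustrative figures rest wholly on assumptions. The conclusion about the definition needs none of them. It rests on the literal wording and on the absence of an as-treated rule in the SAP at hand. The primary endpoint is not affected. The change should be made because it is specific and cheap and concerns the trial's named harms.

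**What to change.** 1. Define the SAF as all randomised patients to whom either trial antiseptic was applied at least once, grouped by the product actually applied.
2. State the group for patients who received both products, and list their events individually.
3. Report the number of patients prepared with a product other than the allocated one, even if it is zero.
4. State that the toxicity and allergy endpoint is analysed on the SAF.

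The cost is about one sentence in the definition, a line on the endpoint, and an actual-treatment variable in the dataset. The Revision History shows that Version 2 changed the analysis sets for peer review, and the subgroup section is partly written in the past tense, so the analysis may already have been run. If so, the cost also includes a dated revision labelled as made after the analysis, and a re-run of the safety tables.

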1. ANALYSIS OF EFFICACY
   1. Analysis Plan for Primary Endpoints

Primary efficacy endpoint is postoperative 30-day SSI. To compare the treatment effects, the adjusted risk ratio and its 95% CI will be estimated using the Mantel-Haenszel method. To test for a significant association with the primary outcome, the Mantel-Haenszel test will be applied after the adjustment for allocation factors.

- 1. Analyses Plan for Secondary Endpoints

The analyses of the secondary efficacy endpoints will be performed to support the discussion on the results of the primary analysis in this trial. Multiplicity adjustment will not be performed in this trial in assessing secondary endpoints.

To compare the treatment effects, the adjusted risk ratio and its 95% CI will be estimated using the Mantel-Haenszel method. To test for a significant association with the primary outcome, the Mantel-Haenszel test will be applied after the adjustment for allocation factors.

Secondary efficacy endpoints

The Mantel-Haenszel test will be applied after adjusting for allocation factors.

1. **Postoperative 30-day superficial incisional SSI rate**
2. **Deep incisional SSI rate, organ/space SSI rate**
3. **Rate of positive bacterial wound culture, and their strains**
4. **Bacterial strain**
5. **Toxicity and allergies events (erythema, symptoms of allergy) rate.**
6. **Reoperation rate due to SSI**
7. SUBGROUP ANALYSIS
   1. Plan for Subgroup Analysis

Subgroup analysis for “Analysis of Efficacy” or “Analysis of Safety” will be performed. We conducted ten (male versus female, age≧65 year-old versus age< 65 year-old, upper gastrointestinal surgery versus lower gastrointestinal surgery versus hepatobiliary surgery, laparoscopy versus laparotomy, obese (Body mass index≧25 kg/m^2^) versus non-obese, ASA≧3 versus ASA<3, blood loss≧100ml versus blood loss<100ml, diabetic versus non-diabetics, malnutrition versus non- malnutrition, smoking versus non-smoking ) subgroup analyses for the primary outcome and secondary outcome (postoperative 30-day superficial incisional SSI) using the Mantel-Haenszel test.

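### The ten subgroup analyses rest on the Mantel-Haenszel test of association alone, so nothing planned tests whether the treatment effect differs between subgroups

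*SAP*

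**What the plan says.** SAP section 7.1 (Plan for Subgroup Analysis) lists ten factors. Nine have two levels, and type of surgery has three: "upper gastrointestinal surgery versus lower gastrointestinal surgery versus hepatobiliary surgery". The method is given in one phrase: "subgroup analyses for the primary outcome and secondary outcome (postoperative 30-day superficial incisional SSI) using the Mantel-Haenszel test". The section names no interaction term, no test of homogeneity and no rule for interpreting results. It does not call the analyses exploratory. One of the factors is "blood loss≧100ml versus blood loss<100ml".

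The section on the primary endpoint shows what the test does in this SAP: "To test for a significant association with the primary outcome, the Mantel-Haenszel test will be applied after the adjustment for allocation factors".

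The general conventions add three relevant entries. On significance, "results from all analysis will be assessed against the significance level(α) of 0.05 and the confidence interval (CI) of 0.95 as two-sided test" unless otherwise noted. On multiplicity, again unless otherwise noted, "statistical adjustments for multiplicity will not be performed in this trial". Under the heading Subgroup Analysis the entry is "Not applicable", which contradicts section 7.1.

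**The concern.** A subgroup analysis asks whether the treatment effect differs between, say, diabetic and non-diabetic patients. The Mantel-Haenszel test asks whether treatment and outcome are associated. Run within one stratum, it gives a p-value for that stratum. Pooled over the strata of a factor, it gives a p-value for a common association. Neither compares the strata with each other. The method named in the SAP's own subgroup section therefore cannot answer the subgroup question.

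At stake is how the results are read. With only within-stratum p-values to go on, a reader tends to compare significant with non-significant strata and infer a difference in effect. Strata are smaller than the whole trial, so such a pattern arises readily when the effect is the same in everyone.

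Blood loss is a separate weakness. It appears to be an operative measurement, known only after randomisation and skin preparation, yet it is listed beside baseline factors. Comparisons within its levels are not fully protected by randomisation.

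**Working it through.** **Inputs from the SAP.** Ten factors (nine two-level, one three-level) and two named outcomes (section 7.1); two-sided 0.05 and no multiplicity adjustment (general conventions). The opening sentence of 7.1 also mentions safety but names no safety outcome for subgroups, so none is counted. The SAP gives no sample size, event rate or power.

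**Reproducing the plan's figure.** Counting the listed factors gives 10, as stated.

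**Number of tests.**
- Strata: 9 × 2 + 1 × 3 = 21.
- Tested within each stratum: 21 × 2 outcomes = 42.
- Pooled over the strata of each factor: 10 × 2 = 20.

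**No effect anywhere, 42 tests.**
- Expected false positives: 42 × 0.05 = 2.1.
- Chance of at least one if the tests were independent: 1 − 0.95^42 = 0.884. They are not independent, because the same patients are split repeatedly and superficial SSI is part of SSI.
- Simulation allowing for that overlap (assumed: N = 600, SSI 15%, 60% of SSIs superficial, balanced independent factors, 500 runs): 2.15 significant tests on average, and at least one in 62.8% of runs (standard error √(0.628 × 0.372 / 500) = 0.022). A second simulation (assumed: N = 600, SSI 12%, superficial SSI 6%, 3,000 runs) gave 63–64%.

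**Same true effect in everyone.** Assume 80% overall power.
- Overall noncentrality: 1.96 + 0.84 = 2.80.
- In each half of an equal split: 2.80 / √2 = 1.98.
- Power in each half: Φ(1.98 − 1.96) = 0.508.
- Chance that exactly one half is significant: 2 × 0.508 × 0.492 = 0.50.

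For an equal split, 2p(1 − p) cannot exceed 0.50, so other overall powers give less. An unequal split follows p₁(1 − p₂) + p₂(1 − p₁) and can fall on either side of 0.50.

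**Simulated uniform effect** (500 runs each, inputs assumed; 20 factor-by-outcome comparisons per trial). Discordant means that at least one stratum is significant and at least one is not.

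| N | Control SSI | Risk ratio | Mean discordant of 20 | Runs with any discordance | Mean significant heterogeneity tests of 20 |
|---|---|---|---|---|---|
| 600 | 15% | 0.6 | 8.6 | 94.2% | 0.86 |
| 1000 | 15% | 0.6 | 9.5 | 97.0% | 0.91 |
| 600 | 20% | 0.5 | 10.0 | 99.2% | 0.92 |

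Discordance is found in 43% to 50% of comparisons (8.6/20 to 10.0/20) with no true difference in effect. Heterogeneity tests flag 4% to 5% (0.86/20 to 0.92/20), close to nominal.

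**After the fix.** 20 interaction tests: 20 × 0.05 = 1.0 false positive expected. The chance of at least one under independence is 1 − 0.95^20 = 0.642.

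**The case against.** The strongest reply is that these are secondary analyses, that the SAP openly says it makes no multiplicity adjustment, and that uncorrected subgroup analyses are common. This stands. The lack of correction is disclosed and is not the main defect, and the proposed 20 tests would also be uncorrected, with about a 64% chance of at least one false positive under independence. The fix addresses what is tested more than how many tests there are.

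It is also fair to say that section 7.1 does not state that each stratum is tested separately. The wording of each contrast makes that the natural reading, but 42 has to stay conditional. The missing interaction test does not depend on it, since pooled tests do not compare strata either.

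A reader might infer more than the SAP supports:
- That some 42 p-values will mislead. Forty-two is the number of tests; about two false positives are expected under no effect.
- That the trial will claim the antiseptic works only in some group. The SAP contains no rule for subgroup claims, so misreading is a risk and not a planned step.
- That "We conducted ten (male versus female" shows the factors were picked after seeing results. The revision history records only the intention-to-treat additions for version 2, made for peer review. The past tense suggests that the analyses may already have been done, but not when the factors were chosen.

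On blood loss, the SAP does not say when it is measured, and no mechanism is evident by which the antiseptic would change it. The timing is an inference, and the size of any bias is unknown.

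**Conclusion.** The concern holds for the missing test of effect modification. This follows from the SAP's text on either reading of section 7.1 and needs no assumption. The count of up to 42 tests, with 2.1 false positives expected under no effect, depends only on within-stratum testing. The figure of about 63% for at least one false positive, the 50% chance of one significant half, and the simulated discordance rest on assumed sample sizes, event rates, power and balanced factors, because the SAP gives none; they show scale and do not predict this trial's results.

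The contradiction between the general conventions and section 7.1 is plain on the page. The blood-loss point is reasonable but minor. The primary analysis is untouched. The plan should be changed because, as it stands, it supplies no valid basis for saying that the effect differs between subgroups.

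**What to change.** In SAP section 7.1:
- For each factor and outcome, report stratum-specific risk ratios with 95% confidence intervals and one treatment-by-factor test. A homogeneity test of the Mantel-Haenszel risk ratios keeps to the SAP's existing framework; a model-based interaction term would also serve.
- Label these 20 tests exploratory and uncorrected, and state that about one false positive is expected.
- State that any subgroup claim rests on these tests and not on within-stratum p-values.
- Show blood loss descriptively only, or document that it is fixed before randomisation.
- Say whether any Mantel-Haenszel test that is kept is run within strata or pooled over them.

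In the general conventions, replace the Subgroup Analysis entry with a reference to section 7.1.

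The cost is SAP wording and a few lines of code. Interaction tests have low power, so fewer subgroup statements will be possible, and a non-significant result will not show that effects are equal. If the subgroup analyses have already been done, the added tests must be labelled post hoc.
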